#### Matching

Patients in the usual care group are consecutively matched with the intervention group according to age (per 5 years age categories), gender and risk group (high CV risk or CVD) at the beginning of the study. Each patient in the intervention group is matched to 2 patients in the usual care group. These patients in the usual care group are randomly selected from the eligible population in practices delivering usual care.

### Study procedures

Patients will be identified at the beginning of the study in order to be able to analyse factors such as mortality and comorbidity during follow-up. The study starts when patients in the intervention group visit the general practice for an intake consultation (t = 0). After the intake visit the 1 yr follow-up period commences. After 1 yr of follow-up, patients are invited for an endpoint visit. A questionnaire will be attached to the invitation letter.

Prior to the endpoint visit, all patients who agree with participation in the study will be asked to fill out the questionnaire at home. The timeline of the study procedures is represented in Fig. 1.

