#### Intervention group

Between September and December 2016 general practices randomly invited eligible patients for an intake visit for the integrated CVRM programme. After 1 yr of follow-up, these patients are invited for the study until enough patients are included. The invitation for the study will be sent just before the yearly follow-up visit in the CVRM programme. This visit will be used as the endpoint visit for the study. Just before this follow-up visit, the patients receive a letter from their GP to inform them about the study. If the patient agrees to participate, informed consent is obtained during the follow-up visit.

Patients will be selected in such way, that 50% will be below 65 years and 50% over 65 years, to achieve a reasonable distribution across age categories.

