#### Usual care group

In order to create the same study population as in the intervention group, we identify patients in the usual care group according to the protocol (‘Organized Practice’) as described before, including systematically screening of the practice population based on ICPC-coded diagnoses and ATC-codes, and manually checking of medical records. As the general practices in the usual care group do not start with the integrated care programme for CVRM, patients in the usual care group will not be invited for an intake consultation at baseline. Subsequently, a risk profile based on complete data on age, sex, smoking status, blood pressure and lipid spectrum may be missing. In that case, patients can be included if the 10-yeas risk is at least 10%, based on the data that are available. For example, a 55-year old male patient with a missing smoking status and missing total cholesterol/ HDL- cholesterol ratio can be classified as having a CV risk > 10% based on a known systolic blood pressure of 160 mmHg.

Patients in the usual care group are matched to patients in the intervention group. Therefore, the patient in the usual care group will only be invited for the study after the patient in the intervention group agreed to participate. Patients in the usual care group will be invited by letter and subsequently by telephone. If this patient does not agree with participation in the study, the second matched patient from the usual care group will receive an invitation. If the second matched patient also does not agree with participation, we will randomly invite one of the remaining patients from the usual care group who were not invited for the study.

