### Sample size calculation

Calculation of the sample size is based on a reduction in SBP and LDL-cholesterol in the intervention group after 1 year of follow-up. We consider a 5 mmHg absolute reduction in SBP and a 0.3 mmol/L reduction in LDL-cholesterol in the intervention group as clinically relevant [5, 31]. We assume that SBP and LDL-cholesterol levels in the usual care group remain stable. To detect these differences we need a sample size of 370 patients in the intervention group. This calculation is based on an alpha of 0.05, a power of 80%, and an intra-cluster correlation coefficient of 0.05 for the general practice cluster level. Furthermore, we take into account the response rate. We expect that the response rate in the intervention group will be 70%. This results in a sample size of 587 patients in the intervention group. The intervention patients are matched to patients from the usual care group. In the usual care group we estimated a lower response rate of 50%, as these patients might be less used to visit the general practice compared to the probably regularly controlled patients in the intervention group. Therefore, each intervention patient will be matched with 2 patients from the usual care group. This results in 587 × 2 = 1174 patients in the usual care group. The intervention group and usual care group are both divided into two groups (patients with CVD and patients with high CV risk) equal in size. The intervention group is selected from 17 general practices and the usual care group from 9 general practices.

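### Only the intervention arm is conditioned on attending a baseline intake, and the named confounders include no measure of prior care-seeking

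*Protocol article*

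**What the plan says.** **Intervention arm.** Between September and December 2016, "general practices randomly invited eligible patients for an intake visit for the integrated CVRM programme" (Recruitment, Intervention group). Study procedures sets the clock at attendance: "The study starts when patients in the intervention group visit the general practice for an intake consultation (t = 0"). Recruitment to the study comes a year later: "The invitation for the study will be sent just before the yearly follow-up visit in the CVRM programme", and "This visit will be used as the endpoint visit for the study".

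**Usual-care arm.** Patients are found by the same code screening and record check, but "patients in the usual care group will not be invited for an intake consultation at baseline" (Usual care group). Under Matching, "These patients in the usual care group are randomly selected from the eligible population in practices delivering usual care". They are invited by letter and then by telephone, and consent is taken at the endpoint visit (Usual care group; Ethical aspects and informed consent).

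**Handling of differences.** Matching is "according to age (per 5 years age categories), gender and risk group (high CV risk or CVD) at the beginning of the study". Statistical analyses names medication use, four comorbidities and practice characteristics as confounders fixed in advance. Outcomes and data collection says that health care use before the study is taken from the medical files. Limitations says that care given before the intervention will be taken into account.

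**The plan's own expectation.** Sample size calculation assumes 70% response in the intervention group and 50% in usual care, because "these patients might be less used to visit the general practice compared to the probably regularly controlled patients in the intervention group".

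**The concern.** The two arms start from the same kind of eligible list but reach the analysis by different routes. An intervention patient must have answered a preventive-care invitation and attended an intake before follow-up begins, and must still be attending a year later. A usual-care patient faces no such test at baseline. People who take up preventive invitations may differ from those who do not in adherence, lifestyle and earlier monitoring, all of which can bear on SBP and LDL-cholesterol.

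The Study aim is the effect of running the programme in general practice on patients with CVD or at high risk, and active invitation is itself an element of the programme (Table 1). An eligible patient who was invited but never came to intake belongs to that aim but has no route into the intervention group. The comparison is closer to programme attenders against a differently filtered sample, so a difference in care-seeking could be mixed into the estimated effect.

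**Working it through.** The article gives no figure for this point, so there is none to reproduce. The check sets the two routes side by side.

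| Step | Intervention | Usual care |
|---|---|---|
| Listing | ICPC/ATC screening, record check | Same protocol |
| Baseline | Invited to intake and attends; this is t = 0 | No intake; random draw, matched |
| End of year | Study invitation tied to the yearly programme visit | Letter, then telephone |
| Consent and outcome | At that programme visit | At the endpoint visit |
| Expected study response | 70% | 50% |

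1. **Where the arms part.** Listing is shared, and so is the need to consent and attend at the end. The unshared step is attendance at baseline.

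2. **What 70% and 50% measure.** Both are expected responses to the study invitation. Neither is uptake of the intake, for which the article gives no rate. Part of the gap may also be caused by a year of regular programme visits. The two figures therefore show that the authors expect different visiting habits, but they do not measure the selection at baseline.

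3. **Form of the bias.** Let q be the share of analysed usual-care patients who would not have attended an intake, and d their mean outcome minus that of the other analysed usual-care patients. Let s be any remaining difference, in the same direction (usual care minus intervention), that arises because the final response filters differ. The shift in the usual-care minus intervention contrast is q × d + s. The article gives none of q, d or s. A positive total favours the programme and a negative one works against it.

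4. **Illustration on assumed values only.** With s = 0, q = 0.2 and d = 3 mmHg in absolute size, the shift is 0.2 × 3 = 0.6 mmHg. With q = 0.4 and d = 5 mmHg it is 0.4 × 5 = 2.0 mmHg. Either sign is possible. Because q applies to people who agreed to attend a visit, the upper value is hard to justify. This is not an estimate for this study.

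5. **What the adjustment covers.** Matching uses age band, gender and risk group. The named patient covariates are blood pressure lowering drugs, anticoagulants, lipid lowering drugs, COPD, heart failure, atrial fibrillation and renal failure. The named practice covariates are disciplines involved, number of patients and number of GPs. Consultations and measurements before the study are not named, although such data are to be collected.

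6. **Which look-back period is usable.** Table 1 and the section on the programme for individual patients place the lipid test before the intake, as part of the programme. A 12-month window ending at t = 0 would thus record LDL for essentially every intervention patient by construction. Setting says practices could join from January 2016, and intake invitations ran from September to December 2016. For a practice that joined in January, that is 8 to 11 months of possible programme activity before the invitation. The window has to close earlier. Usual care also needs a corresponding date, since t = 0 is defined only by the intervention intake.

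**The case against.** The strongest reply is that the analysed comparison is attenders against attenders, filtered at different times. Usual-care patients count only if they accept an invitation and consent at an endpoint visit, and half are expected to decline. Their list is also partly selected on contact: they need a coded diagnosis or prescription, risk management in primary care and, where the risk profile is incomplete, enough recorded data to reach the 10% threshold. A reader might infer that people who never attend sit in the usual-care results. The documents do not support that. This part of the reply stands and narrows the gap, but it does not close it, because only one arm is conditioned on attendance at baseline.

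The second reply is that adjustment is not absent. Medication use is a partial, weak proxy for engagement, the covariate list is worded as examples, and Limitations promises to allow for prior care. A reader might infer that the model ignores care-seeking altogether, and that is too strong. However, the promise follows a remark about differences between practices within the intervention group, and the list fixed in advance names no term that would carry it out.

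The third reply is that the sentence on recruitment could be read as inviting everyone who was invited to intake. Study procedures starts follow-up after the intake visit, and the endpoint visit is a programme follow-up visit, so that reading does not hold.

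**Conclusion.** The point holds in a limited form. Entry is unequal at baseline, the article itself expects the groups to differ in visiting habits, and the named confounders include no measure of this, although the data are to be collected and an intention to allow for prior care is stated. The size and direction of any bias cannot be derived. A lower response in usual care could leave a more health-conscious group there, which would work against the programme.

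Two stronger conclusions are tempting. One is that a favourable result would be an artefact of attendance; no figure in the article supports this. The other is that intervention-practice patients who declined intake go uncounted. The article is silent on such counts, and participant flow is something a design article may leave to the full protocol or the results report.

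The conclusion assumes that the confounder list is meant to be substantially complete, as its description as defined in advance suggests. The recruitment structure cannot readily be changed, but the analysis and the claim can, so this should be corrected.

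**What to change.** - **Confounders.** Under Statistical analyses, add the number of GP/PN contacts and whether SBP and LDL were recorded, each over a 12-month window.
- **Window.** Close it before any programme activity: before the practice's programme start, or before the patient's programme invitation and pre-intake laboratory test. Apply the same calendar window to the matched usual-care patients. A usual-care patient invited as a replacement takes the window of the intervention patient whose match they fill.
- **Claim.** State in the aim and conclusion that the estimate applies to patients who take up and remain in the programme, not to all eligible patients in practices that run it.

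The cost is a little more abstraction from files that are already being searched, and a narrower claim. Measured contacts will reduce a difference in care-seeking but may not remove it, so the narrower claim is needed alongside the added covariates.

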**Fig. 1 Fig1:**
[figure not shown]
Schedule of enrolment, interventions, and assessments. *These baseline variables are collected retrospectively after one year of follow-up

#### Ethical aspects and informed consent

General practices in both groups will not be informed about which patients are identified at baseline to prevent any influence on their management. Consequently, it will not always be possible to take into account the life expectancy, cognitive function and language skills of the identified patients at baseline, as information on these exclusion criteria is not always adequately registered in the medical records. Just before the end of follow-up, GPs will be informed about the identified patients and asked to assess these exclusion criteria.

Also, at baseline patients in both groups will not yet be informed about the study to prevent that they are aware of being observed and modify their behaviour (Hawthorne effect). Based on the Dutch law for data protection, obtaining informed consent for the identification of patients is not necessary. All obtained data (age, gender and risk category) during the identification will be processed pseudo anonymised and the key to the data will be kept within the general practices. The researchers do have access to this information. Baseline data will be collected retrospectively for all patients as patients are not invited for a baseline visit in the context of the study.

Written informed consent is obtained by the GP or PN during the end-point visit and includes an agreement stating that he or she i) is sufficiently informed, had the opportunity to ask additional questions and had enough time to make a decision; ii) agrees with voluntary participation and at any time can withdraw from participation; iii) agrees with use of medical data and data of questionnaires for the purposes described in the information form; iv) agrees with the storage of the study data for 15 years after this study.

The study was reviewed by the Isala hospital Review Board and exempted from full assessment under the Medical Research Involving Human Subjects Act on the 16th of June 2016 (reference number 16.06104).

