### Limitations

One limitation is the lack of random allocation to the two arms. This might lead to differences in practice characteristics between the intervention group and the usual group, and lead to either an over- or underestimation of the effect of integrated care for CVRM, when these differences are not adequately adjusted for. Besides, there may be differences in given care before implementation of integrated care for CVRM between different practices within the intervention group. This could also influence the effect of integrated care of CVRM. However, due to the complete registration of patient data in the Dutch general practice information system, we will be able to accurately collect patient data on years prior to the study and take into account the given care prior to the intervention. Furthermore, ample measures have been taken (notably matching of patients, multivariable analyses) to prevent confounding in our study.

Since patients will be selected from different general practices, we have to deal with a cluster effect. The intervention under study may be heterogeneous [40]. For example, differences in practice size, practice facilities and space, training of GP and staff, availability of supportive staff, time-management, attitude towards prevention and the GP-patient relationship might lead to cluster-level differences.

Another limitation of our study design is that it is not possible to blind GPs, PNs and participants for the intervention. Blinding is impossible due to the nature of the intervention. To minimize bias and maximize the validity of the results, participants are selected just before the end of the study. Also, during follow-up the general practices are not informed about which patients are identified as eligible to participate in the study.

A disadvantage of the regional approach of our study is the risk of contamination between the usual care group and the intervention group. Usual care may change in the direction of the intervention and therefore the effect of the intervention may be underestimated. However, as GPs in the usual care group do not use the guideline for the implementation of integrated care for CVRM, do not register patient data in an information system for integrated care, and yearly benchmark meetings are not mandatory, we expect the effect of contamination to be minimal. We will collect data on provided CVRM care to assess contamination.

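### Unblinded GPs judge life expectancy and cognition at one year with no reference to t=0, and consent follows at the endpoint visit, so morbidity and mortality can be selected on what happened during follow-up

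*Protocol article*

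**What the plan says.** All references are to the protocol article.

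- **Purpose of early identification** (Study procedures, opening sentence): "Patients will be identified at the beginning of the study in order to be able to analyse factors such as mortality and comorbidity during follow-up".
- **Exclusions** (ZWOT-CASE study population): limited life expectancy and cognitive impairment are both left to the GP's judgement.
- **Timing of that judgement** (Ethical aspects and informed consent): practices are not told who has been identified, so "it will not always be possible to take into account the life expectancy, cognitive function and language skills of the identified patients at baseline". The remedy is: "Just before the end of follow-up, GPs will be informed about the identified patients and asked to assess these exclusion criteria". No reference date is given.
- **Blinding** (Limitations): "it is not possible to blind GPs, PNs and participants for the intervention".
- **Consent** (Ethical aspects and informed consent): "Written informed consent is obtained by the GP or PN during the end-point visit". The patient then "agrees with use of medical data and data of questionnaires for the purposes described in the information form". Of the identification stage the article says: "All obtained data (age, gender and risk category) during the identification will be processed pseudo anonymised".
- **Outcomes** (Table 7): newly developed CVD is secondary endpoint 7, developed comorbidity 8, mortality 9.
- **Entry to the study**: intervention patients have attended an intake visit, which defines t=0. Usual-care patients are found by the same screening protocol, with a manual records check, but have no intake visit. Expected response is 70% in the intervention group and 50% in usual care.

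**The concern.** An exclusion that is meant to describe a patient at entry should not depend on what happens after entry. Here the GP is asked a year later, knowing both the arm and the patient's course, and nothing in the wording directs the GP back to t=0. A patient who was fit at the start and is now cognitively impaired or terminally ill may have had one of the outcomes that the study counts, and the same fact can remove that patient as ineligible. Consent at the endpoint visit adds a second gate, which only living attenders pass.

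At stake are outcomes 7 to 9. Selection that is equal in the two arms understates event risks. Selection that differs by arm distorts the comparison. The participants who pass these gates also supply the SBP and LDL-cholesterol comparison, so the selection is not confined to secondary endpoints, although outcomes 7 to 9 are where it acts directly.

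**Working it through.** **1. Order of events.** Identification at t=0 (age, gender, risk category), one year of care, GP check of the exclusions, then endpoint visit with consent.

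**2. Following patients through the rule as written.**

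- *Limited life expectancy at t=0 and recorded:* can be excluded at baseline in either arm, because both have a manual records check.
- *Limited life expectancy at t=0, not recorded, alive at one year:* excluded by the late check, as intended.
- *Limited life expectancy at t=0, not recorded, died during the year:* the article does not say how the late check applies.
- *Fit at t=0, then terminally ill or cognitively impaired during the year:* can be excluded by the late check, even if the cause was outcome 7 or 8.
- *Fit at t=0, died during the year:* can appear only in the identified cohort, never among the consenting attenders.

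The third and fourth groups show the problem. The rule can remove a patient whose illness came after t=0, and it is undefined for one whose illness came before.

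**3. Consented set.** Consent requires attending the endpoint visit, so deaths before that visit are 0 of 370 and 0 of 370 by construction.

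**4. Identified cohort.** Sample size calculation gives 587 intervention and 587 × 2 = 1174 usual-care patients. The doubling reproduces. The 587 does not follow from the stated response rate alone: 370 / 0.70 = 529, and 370 / 0.70 / 0.90 = 587.3 would need a further 10% loss that the article does not mention. The point here does not depend on this. The article gives no death rate. Over an assumed one-year mortality of 0.5% to 3%:

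- intervention: 587 × 0.005 = 2.9 to 587 × 0.03 = 17.6, about 3 to 18 deaths;
- usual care: 1174 × 0.005 = 5.9 to 1174 × 0.03 = 35.2, about 6 to 35 deaths.

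All of these are lost if only consenting attenders are analysed.

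**5. Morbidity, illustration only.** Let the true event risk p be the same in both arms, and let a fraction f of patients with events be lost through late exclusion or non-attendance. The observed risk is p(1 − f) / [p(1 − f) + 1 − p]. Both p and f are assumptions.

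- p = 2%, f = 20% in both arms: 0.016 / 0.996 = 1.61% in each. The risk ratio is 1.0, but the risk is understated.
- p = 2%, f = 20% intervention and 40% usual care: 1.61% against 0.012 / 0.992 = 1.21%, risk ratio 1.33.
- Losses the other way round: risk ratio 0.75.
- p = 4%: the last two ratios become 1.32 and 0.76.

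Unequal loss is plausible because intervention patients have already attended an intake visit and expected response differs (70% against 50%). The documents do not fix its direction or size.

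**The case against.** Keeping practices unaware of who was identified is a reasoned protection against altered management, and it is why the check comes late. Lack of blinding is disclosed. The deferral covers only criteria that the records could not settle at baseline. The wording does not forbid a GP from judging status at t=0. The outcomes concerned are secondary, and analysis sets are commonly left to an analysis plan that is not shown. All of this stands, and the missing denominator is not by itself the point. What remains is a stated rule: an unblinded judgement made at one year, with no reference date, on criteria that an outcome event can bring about.

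Four stronger readings are tempting and are not supported.

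- *Mortality will be analysed only in survivors.* Study procedures says that identification at the start is there "in order to be able to analyse factors such as mortality and comorbidity during follow-up". The zero count applies to the consented set. The article does not say that mortality is confined to it.
- *One arm is screened at t=0 and the other at one year.* Both arms have a records check and both have the late GP check. Only the attended intake differs.
- *A block of high-risk patients sits in usual care alone.* Taking 1% to 2% of 1174 gives 12 to 23 patients, but the prevalence is assumed. The figure also ignores the records check in usual care and supposes that there are no such patients in the intervention arm.
- *Adjusted models cannot include those who died.* The identification data are limited to three items, but the same section plans retrospective baseline collection for all patients. Whether records may be used without consent is not stated either way.

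**Conclusion.** The point holds in a limited form. For criteria not settled from the records at baseline, the late check allows exclusion after an outcome event by GPs who know the arm. Consent at the endpoint visit makes the consented set one of surviving attenders. Neither feature is reconciled with the stated purpose of identifying patients at the start. The consequence is possible bias in outcomes 7 to 9, and some selection of the participants in the primary comparison.

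Only one size follows from the text: no deaths before the visit among the 370 + 370. The death counts and the risk ratios of 0.75 to 1.33 rest on assumed mortality, event risk and loss, and show what could happen rather than what is expected. The direction is unknown. The change is worth making, but the point does not show that the mortality outcome is empty or that the study is invalid.

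**What to change.** In Ethical aspects and informed consent:

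- Ask GPs to judge these exclusions as they stood at t=0, which for usual care is the matched partner's intake date. They should use record entries dated before t=0, plus their own knowledge where the records are incomplete. Dated entries alone will not do, since the article gives inadequate registration as the reason for the late check.
- Keep in the identified cohort any patient whose condition arose after t=0.

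In Statistical analyses:

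- Count mortality in all identified patients of both groups, and new CVD and comorbidity likewise where records may be used. Adjust for age, sex and risk group, plus the prespecified covariates where available.
- Report late exclusions, deaths and non-consent by arm, with reasons.
- Describe morbidity results from the consented set as applying to surviving attenders.

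The cost is small, because the GP check and the retrospective record review already take place. The downsides are that GP recall may be needed, and that adjustment may be limited for patients without consent.
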